## Abstract

**Introduction:**

Glycemic dysregulation is a hallmark of type 2 diabetes (T2D) and contributes to skeletal muscle (SKM) loss and frailty risk, especially in older adults. Glycemic control and physical function are supported by SKM capillarization and mitochondrial function, and their impairment contributes to T2D development. While high-intensity interval training (HIIT) is a promising intervention, adherence and effectiveness remain concerns for prescribing HIIT among older adults at risk for T2D. Local heat therapy (LHT) may be a more practical initial strategy to improve SKM architectural factors and precondition SKM, enhancing physiological adaptations to exercise in this population.

**Methods and analysis:**

Heat and Exercise in Aging as Therapy (HEAT) is a two-phase, randomized, sham-controlled clinical trial investigating the efficacy of LHT to improve glycemic control and decrease frailty risk via improved SKM architecture among older adults with prediabetes. LHT is tested as a standalone intervention and as a means to precondition SKM for subsequent HIIT, improving exercise adaptations. In Phase 1, LHT and sham (CON) groups apply heat pads for 90 minutes/day, 6 days/week, for 12 weeks. A separate HIIT group completes 4x4-minute cycling intervals at 90–95% VO₂peak, 3 days/week. In Phase 2, LHT and CON groups begin HIIT. Participants (≥50 years) have impaired fasting glucose (100–125 mg/dL) and/or HbA1c (5.7–6.4%). Biospecimen collection and clinical assessments occur at baseline (T1), after Phase 1 (T2), and Phase 2 (T3). To our knowledge, this is the first study to determine the use of local heat pad on pre-diabetic older population. If successful, LHT may be a practical, scalable, non-invasive intervention to improve glycemic control and reduce frailty risk in older adults with prediabetes, preventing progression to T2D.

## Introduction

Skeletal muscle (SKM) metabolic function is dysregulated in type 2 diabetes mellitus (T2D). This dysregulation is associated with changes in muscle architecture which contribute to phenotypic frailty including slow gait speed, weakness, unintentional weight loss, fatigue, and low physical activity levels [1]. Glycemic dysregulation (e.g., insulin resistance) is a hallmark of T2D and contributes to SKM loss in adults with diabetes [2]. The pathogenic development of insulin resistance in T2D is multifaceted and includes, but is not limited to, mitochondrial dysfunction [3,4], decreased capillarization [5,6], and decreased SKM mass [7,8]. Evidence suggests that capillary networks and mitochondria-mediated metabolic alterations occur before the development of overt T2D; thus, it is critical to explore potential therapies in individuals with prediabetes to decrease T2D risk.

Exercise training is a key strategy to manage metabolic disease and decrease T2D risk [9]. While different exercise modalities improve SKM health across age groups, high intensity interval training (HIIT) can improve capillary density [10,11], mitochondrial content and function [12–14], and SKM mass [15] in older adults and those with T2D and obesity. However, exercise adherence is low [9,16,17]. In older adults at risk for T2D, compromised oxygen delivery and mitochondrial dysfunction [18] promote exercise intolerance, a factor contributing to low exercise adherence [19]. Alternative means to manage metabolic disease and improve metabolic health are needed, and heat therapy is a possible solution.

Repeated exposure to whole-body and local (e.g., thigh) heat therapy (LHT) improve mitochondrial biogenesis, muscle capillarization, glycemic control, and increase whole-muscle and muscle fiber cross-sectional area (CSA) [20]. Of particular interest, repeated whole-body heat therapy and moderate-intensity continuous exercise training in young, sedentary adults similarly increased SKM capillary density, capillary-fiber perimeter exchange index, aerobic capacity, and insulin sensitivity [21]. Moreover, whole-body heat therapy can decrease fasting glucose and insulin levels in sedentary, overweight men exposed to temperatures of 34–39°C for 1–6 hrs across 10 sessions and in obese rats exposed to 38°C for 30 minutes, three times per week, for 12 weeks [22–25]. Recent evidence shows that repeated exposure to local (e.g., thigh) and whole-body heat therapy alone improves mitochondrial biogenesis (i.e., PGC-1α and respiratory chain complex expression) [26], muscle capillarization (e.g., vascular endothelial growth factor [VEGF], angiopoietin 1, and capillary density) [20,27,28], glycemic control (e.g., fasting glucose and insulin), and increases whole muscle and muscle fiber cross-sectional area (CSA). Mechanistically, heating the thighs alone using hot water (48–52°C) perfused through tubing to raise leg skin temperature to 39–40°C without altering core temperature increased VEGF, angiopoietin 1, and heat shock protein (HSP) mRNA expression [29]. These data suggest that heat therapy could be an effective treatment to improve glycemic control and metabolic disease-induced muscle atrophy, thus reducing the risk of T2D and frailty.

The magnitude of angiogenic adaptations to local heat therapy (LHT) can be similar to whole-body heating [29], providing a foundation to support examination of the therapeutic potential of LHT. Although it has not been examined in individuals with prediabetes, a single lower body exposure to hot water circulation at 43°C for 90 min in patients with peripheral artery disease tended to improve walking performance [30]. Given these promising initial findings, LHT may be useful to improve muscle architecture (i.e., capillarization, mitochondria, muscle fiber CSA). Such changes could improve exercise tolerance by preconditioning the microenvironment of SKM, likely enhancing exercise adherence and improving subsequent exercise adaptations. Therefore, changes in the SKM with LHT alone, and with exercise training following LHT, may improve glycemic control and physical function, thereby decreasing risk for T2D and frailty, in older individuals.

Strong evidence supports the benefits of heat therapy on SKM and glycemic control. However, the efficacy of LHT to decrease risk for T2D and frailty in older adults with prediabetes has not been examined. Therefore, we developed the Heat and Exercise in Aging as Therapy (HEAT) study. This randomized, controlled clinical trial aims to evaluate the effectiveness of LHT among older adults with prediabetes using a two-phased approach. The aim of Phase 1 is to compare the effectiveness of LHT alone versus HIIT to improve muscle architecture, glycemic control, exercise capacity, and risk of frailty (Aim 1). The aim of Phase 2 is to assess whether a period of LHT preceding the initiation of HIIT improves exercise responsiveness, resulting in further improvements in SKM architecture, glycemic control, and risk of frailty (Aim 2). Given the practicality and ease of LHT application, findings can be easily translated to clinical recommendations.

## Methods

### Study overview

The Heat and Exercise in Aging as Therapy (HEAT) clinical trial is a two-phase, randomized, sham-controlled, parallel-design study examining the effects of LHT alone, and LHT applied prior to HIIT, on SKM architecture, glycemic regulation, frailty risk, and exercise capacity in older adults with prediabetes (Clinical Trial NCT06580964 [https://clinicaltrials.gov/study/NCT06580964]). Eligible participants are randomized to one of three intervention groups for Phase 1 of the study: HIIT alone (HIIT group), LHT followed by HIIT (LHT group), or sham heat pad followed by HIIT (control [CON] group; thermoneutral temperature).

All primary outcome measures are assessed at baseline (timepoint [T]1), after Phase 1 (T2), and after Phase 2 (T3). Phase 1 consists of 12 weeks of the LHT intervention for the LHT and CON groups, or 12 weeks of high-intensity interval training for the HIIT group. Following T2, only participants in the LHT and CON groups progress to Phase 2, which involves 12 weeks of high-intensity interval training. Participants assigned to the HIIT group conclude their participation in the study after T2. The schedule of enrollment, interventions, and assessments is presented in **Fig 1**, in accordance with SPIRIT guidelines (**S1 Table**). An overview of the study design is presented in **Fig 2**. This study is approved by the Texas Tech University Institutional Review Board (IRB #2024-365) (**S1 File**). Any future modifications to the protocol will be submitted for IRB review and approval prior to implementation, reported to the study safety officer, and documented in the manual of procedures. The first participant will be enrolled on July 31^st^, 2025. Participant enrollment is expected to conclude by July 2028, data collection will be completed by February 2029, and study results are anticipated by December 2029.

**Fig 1 pone.0351577.g001:**
[figure not shown]
The schedule of enrollment, interventions, and assessments.

**Fig 2 pone.0351577.g002:**
[figure not shown]
An overview of the study design.

### Power analysis

A power analysis was performed using G*Power (version 3.1.9.4). Because capillary-fiber perimeter exchange index (CFPE) is a widely measured variable and an important component of anticipated adaptations, we used the results from Kim et al.[27] to power this study. They observed significantly greater CFPE with LHT vs CON (d > 1.5). We used a more conservative, d = 1.2 (reduced by 20%), because older adults might have a blunted response to LHT. We used the statistical analysis of Aim 1 to power the study because it involves more groups (three) and thus requires the largest number of participants. The one-way ANOVA with three groups (d = 1.2, f = 0.4899, α = 0.05) will require 45 total participants (15 per group) to achieve 80% power. This will be followed by two non-orthogonal planned contrasts (CON vs. LHT, LHT vs. HIIT). These *t*-*t*ests (d = 1.2, α = 0.05/2 [Bonferroni]) also require 15 participants per group to achieve 80% power. In the statistical analysis of Aim 2, only two of the three groups are included, leading to greater statistical power. The planned *t*-*t*est (d = 1.2, a = 0.05, 15 participants per group) will achieve 89% power. If needed, the one-way ANOVA with two groups (d = 1.2, a = 0.05, 15 participants per group) will also achieve 89% power. Comparing this number of participants per group to previously published work examining LHT and SKM mitochondria, capillarization, and size [26–28], 15 participants per group is a comparable estimate of sample size. Although not identical to our proposed work, sample sizes of 10 (within-subjects) [23] and 18 (9 per group, between-subjects) [31] were sufficient to detect improvements in glycemic control in overweight men and in obese women with polycystic ovarian syndrome, respectively, in response to whole-body heat therapy. Our power analysis and previously published research support a target sample size of 15 participants per group (CON, HIIT, and LHT). Accounting for a potential 18% attrition rate, we aim to enroll 18 participants per group (9 men, 9 women) for a total target enrollment of 54 participants.

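### The 80% power stated for LHT vs HIIT rests on an effect size taken from LHT vs sham, and the f used for the ANOVA implies a smaller difference for at least one of the two planned contrasts

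*Protocol article*

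**What the plan says.** Everything on sample size is in the Power analysis section of the protocol article. The powering variable is the capillary-fiber perimeter exchange index (CFPE). The effect size comes from one cited study of local heat: "They observed significantly greater CFPE with LHT vs CON", with d above 1.5, cut by 20% to d = 1.2.

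This d is then used in two places for Aim 1:

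- The three-group one-way ANOVA, with d = 1.2, f = 0.4899 and alpha 0.05, "will require 45 total participants (15 per group) to achieve 80% power".
- The two planned contrasts (CON vs LHT, LHT vs HIIT), t-tests with d = 1.2 and a Bonferroni alpha of 0.05/2, "also require 15 participants per group to achieve 80% power".

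The section gives no assumed mean for any arm and no separate effect size for LHT vs HIIT. The end of the Introduction gives the aim of Phase 1 as to "compare the effectiveness of LHT alone versus HIIT to improve muscle architecture", among other outcomes. The Statistical analyses section describes Aim 1 as both comparisons, LHT with CON and LHT with HIIT.

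**The concern.** One effect size, observed for heat against a control, is applied unchanged to a comparison of two active arms. The f chosen for the ANOVA corresponds to a pattern of three means in which the two contrasts cannot both be 1.2. The same paragraph therefore works from two different pictures of the three arms.

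LHT vs HIIT is one of the two stated Aim 1 comparisons. A reader of the protocol will take it to have 80% power. If the true difference between the arms is well below 1.2 SD, the power is far lower, and the document gives no sign of this.

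**Working it through.** **Inputs, all from Power analysis:** d = 1.2; f = 0.4899; N = 45, or 15 per group; alpha 0.05 for the ANOVA and 0.025 per contrast. Two-sided testing is an assumption, because sidedness is not stated; it reproduces the section's own figures.

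**Step 1. Reproduce the stated figures.**

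- ANOVA: noncentrality N·f² = 45 × 0.24 = 10.8 with 2 and 42 df gives power 81.7% (78.6% at N = 42).
- Contrast: noncentrality d·√(n/2) = 1.2 × √7.5 = 3.29 with 28 df and alpha 0.025 gives power 81.5% (78.2% at n = 14).
- Aim 2 t-test: the same noncentrality with alpha 0.05 gives 88.7%, stated as 89%.

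Each figure is right for its own input.

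**Step 2. What f = 0.4899 implies.** With equal groups, f is the SD of the three group means (divisor 3) in units of the within-group SD.

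- Means 0, 0.6, 1.2: f = √[(0.36 + 0 + 0.36)/3] = √0.24 = 0.4899. This is the stated value, 1.2/√6.
- Put CON = 0, LHT = 1.2 and HIIT = x, and require f² = 0.24. This gives 2x² − 2.4x + 0.72 = 0, whose only (double) root is x = 0.6. LHT vs HIIT is then d = 0.6.
- If CON is the middle arm, CON vs LHT is 0.6. If LHT is the middle arm, both contrasts are 0.6.

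**Step 3. What makes both contrasts 1.2.**

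- HIIT equal to CON (0, 1.2, 0): f = √[(0.16 + 0.64 + 0.16)/3] = √0.32 = 0.566.
- LHT midway (0, 1.2, 2.4): f = √[(1.44 + 0 + 1.44)/3] = √0.96 = 0.980.

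Neither is 0.4899. If the range of 1.2 is dropped and only f = 0.4899 is kept, the smaller contrast is largest when CON = HIIT. Then d = 0.4899 × 3/√2 = 1.04, and power is 68% (70% with the pooled 42 df). No set of means with the stated f gives 80% for both contrasts.

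**Step 4. Power of LHT vs HIIT over a range.** Here n = 15 per group, two-sided alpha 0.025, 28 df. The protocol gives no LHT–HIIT difference, so every row is an assumption.

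| True d, LHT vs HIIT | Power |
|---|---|
| 1.2 | 81% |
| 1.0 | 65% |
| 0.8 | 44% |
| 0.6 (pattern matching the stated f) | 25% |
| 0.3 | 7% |

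Using the pooled ANOVA error (42 df) changes little: 26% at d = 0.6. If all 18 enrolled per group were retained, power at 0.6 would be 31%. The smallest d with 80% power is about 1.18.

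**Step 5. Precision.** The half-width of the Bonferroni-adjusted interval is t(0.9875) × √(2/15). This is 2.325 × 0.365 = 0.85 SD with 42 df, or 2.368 × 0.365 = 0.86 SD with 28 df.

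**The case against.** The best defence is that f = 0.4899 is the smallest f compatible with a largest pairwise difference of 1.2. On that reading it is a conservative choice for the omnibus test and not a statement that the third mean lies at the midpoint. The contrast sentence is also conditional: its d and alpha stand beside the result, and the result is correct for them. With means 0, 1.2, 0 the ANOVA has 91.6% power and each contrast 81.5%. With 0, 1.2, 2.4 the ANOVA exceeds 99.9% and each contrast again has 81.5%. So there are patterns in which 15 per group is enough for all three tests.

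This stands as far as it goes. A reader might infer that the stated powers are mutually impossible, or that the section contains a calculation error. The document does not support either, because it never fixes the three means. Nor does it support 25% as the power of LHT vs HIIT; that figure belongs to one pattern. With CON vs LHT at 1.2 and HIIT 0.2 or 0.4 SD above CON, the difference is 1.0 or 0.8 and power is 65% or 44%.

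The defence does not supply a reason to expect 1.2 SD between LHT and HIIT. The first rescuing pattern needs HIIT to do no better than sham, whereas the Introduction says that HIIT can improve capillary density. The second needs HIIT to be 2.4 SD from CON, which the protocol nowhere suggests. The Introduction also reports that whole-body heat and moderate continuous exercise raised CFPE to a similar degree. That was in young adults and with different forms of heat and exercise, so it is only indirect, but it points towards a smaller difference.

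**Conclusion.** The point holds as a question of support. The 80% power is shown for CON vs LHT at d = 1.2. It is not shown for LHT vs HIIT, where the effect size is borrowed from another comparison and the f in the same section corresponds to a pattern with at least one contrast at 0.6. Depending on the true LHT–HIIT difference, power runs from 81% at 1.2 SD to 7% at 0.3 SD. It reaches 80% only from about 1.18 SD upwards. These figures assume 15 analysed per group, two-sided tests at 0.025, normal change scores and equal variances.

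A reader might go further and infer that the trial means to present a non-significant LHT–HIIT result as equal effectiveness, and that an equivalence margin is therefore missing. The document makes no equivalence or non-inferiority claim, so that inference is not supported and the point does not need it.

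**What to change.** In the Power analysis section:

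1. Limit the 80% claim to CON vs LHT at d = 1.2.
2. State the assumed CFPE change in all three arms, so that the f for the ANOVA and the d for each contrast come from one set of means.
3. Give the power of LHT vs HIIT as a range, labelled as an assumption, using the values tabulated above, and state the smallest detectable difference of about 1.18 SD.
4. Say that this contrast will be reported with its confidence interval, whose expected half-width is about 0.85 SD.

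The cost is a few sentences. No participants are added and the analysis does not change. The downside is a less favourable stated power for LHT vs HIIT. Powering that contrast at d = 0.6 would take about 55 per group, which is why restating the claim is the practical course.

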### Settings

This study takes place in the Department of Kinesiology and Sport Management facility at Texas Tech University in Lubbock, TX, USA. This is an academic research setting equipped with exercise, clinical, and biochemical laboratories.

### Recruitment, consent, screening, and group allocation

Potential participants are invited to voluntarily join the study. Recruitment efforts include posting study flyers in local pharmacies, supermarkets, and at relevant community events, and posting electronic advertisements on listservs and social media. Social media announcements specify targeting older adults (50+) in the Lubbock, TX area.

#### Initial phone pre-screening.

Potential participants undergo telephone pre-screening to determine preliminary eligibility. During this pre-screening, participants must confirm being informed by a physician that they have prediabetes, may be at risk for developing diabetes, or exhibit elevated blood glucose levels. Additional eligibility criteria include leading a sedentary lifestyle [32,33], absence of medical conditions that could limit participation in HIIT, no heavy alcohol consumption, no use of nicotine or cannabis products, and not currently taking medications known to influence intervention outcomes (**Table 1**).

**Table 1 pone.0351577.t001:** Inclusion and exclusion criteria for the HEAT study.

Inclusion	Exclusion
• Age ≥ 50 years of age • Structured exercise < 30 minutes, 3x/week • Body mass ≥ 110 lbs • Fasting blood glucose 100–125 mg/dL and hemoglobin A1c 5.7–6.4% • Consume <8 (women) or <15 (men) alcohol-containing beverages per week • Do not use nicotine or cannabis • Do not take any medications that could interfere with responses to the interventions (e.g., corticosteroids, opiates, benzodiazepines, tricyclic antidepressants, beta blockers, sulfonylureas, insulin, metformin, anticoagulants, barbiturates, insulin sensitizers, fibrates, immunosuppressants)	• History of peripheral neuropathies • Medical complications that could contraindicate participation in the high intensity interval training intervention including: orthopedic complications that would limit your ability to perform cycling exercise, significant cardiovascular impairments (e.g., history of arrhythmias, severe uncontrolled hypertension, etc.), diagnosed metabolic disease (e.g., diabetes), renal disease, sickle cell anemia, or cancer in remission for <6 months • Known history of slow wound healing • Allergy to lidocaine or latex • Pregnancy • > 1.5” subcutaneous fat over the thigh muscle. • Symptoms suggestive of cardiovascular, respiratory, metabolic, or renal diseases including discomfort, pressure, or pain in your chest, neck, jaw, arms, calves, or other areas potentially related to ischemia; shortness of breath at rest or with mild exertion; dizziness or fainting (syncope); difficulty breathing while lying flat (orthopnea) or sudden nighttime breathing difficulties (paroxysmal nocturnal dyspnea) • Palpitations or rapid heartbeat (tachycardia); pain or cramping in legs during physical activity (intermittent claudication); a known heart murmur; swelling in ankles (edema); unusual fatigue or shortness of breath during routine activities or at rest

#### Consent/screening visit.

After pre-screening, potential eligible participants are invited for a consent and screening visit. Participants are asked to fast (no food or drink except water) for at least 12 hours before this visit. After a thorough explanation of the study procedures, risks, and benefits by the clinical research coordinator, participants must demonstrate understanding of the study before providing written informed consent. Following the written informed consent, blood pressure is measured twice, with a third measurement if either systolic (SBP) or diastolic (DBP) blood pressure differs by >5 mmHg between the first two measurements [34]. Fasting blood glucose (FBG) and hemoglobin A1c (HbA1c) levels are measured to confirm fasting dysglycemia (FBG 100–125 mg/dL) and/or elevated HbA1c (5.7–6.4%), indicative of prediabetes [35]. Then, they complete medical and physical activity history questionnaires (International Physical Activity Questionnaire [IPAQ] [36]). Full inclusion and exclusion criteria are listed in **Table 1**. Participants receive compensation for all testing procedures, exercise sessions, and weekly laboratory visits.

#### Randomization and stratification.

Participants are stratified based on sex assigned at birth (male, female), age brackets (e.g., 50–59, 60–69 years, 70–79, etc.), and glucose tolerance (glucose concentration at the 1-hour blood draw following ingestion of 75 g glucose: < 155 mg/dL, normal glucose tolerance; 155 to <209 mg/dL, intermediate hyperglycemia; and ≥209, potential T2D) [37] at baseline. A permuted block randomization method [38] with a block size of three (1:1:1 ratio) is used within each stratum to ensure balanced allocation among groups (CON, HIIT, LHT). Accordingly, an allocation table is used to randomize participants to groups. Group assignments are recorded in a separate randomization form, accessible only to a designated unblinded investigator, on the HIPAA-compliant Research Electronic Data Capture (REDCap)2 database, adhering to NIH guidelines for clinical trials. This balanced permuted block randomization can ensure baseline comparability between treatment groups, allow further analysis of treatment effects for different subgroups, and maximize statistical power.

